**Methods:**

One hundred and thirty patients diagnosed with POP–Q II–III and concomitant SUI requiring surgical treatment will be included in this prospective, randomized, double-blind, controlled clinical trial. Patients will be randomly allocated to receive either original TVM (TVM group, *n* = 65) or modified TVM surgery (mTVM group, *n* = 65). As the primary outcome parameter, we will evaluate the objective SUI and POP cure rates. Secondary endpoints include postoperative morbidity as assessed with the International Urogynaecological Association classification and subjective prolapse and incontinence cure rates reported by questionnaires.

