### Primary endpoints

The primary outcome measures will be a significant improvement in POP repair and objective cure of SUI after the surgery. The efficacy of POP repair will be understood as a significant (> 3 cm) improvement during follow-up at points Aa, Ba, C, and D using the POP–Q system (International Continence Society) [19, 20]. Anti-incontinence efficacy is classified as no further SUI, as diagnosed by cough tests and urodynamic examinations. Besides the gynecological and urodynamic examinations, sonographic findings from introital ultrasound examinations will be analyzed in terms of anatomical success both before and following surgery and during follow-up.

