### Secondary and tertiary endpoints

The secondary measurement outcome will comprise the intraoperative findings and postoperative factors. As concerns the long-term postoperative complications of the mesh procedures, we will determine the extrusion rate, the presence of de novo urge symptoms (DNUS) or urinary tract infection (UTI), and the need for reoperation. The diagnosis of DNUS will be set if detrusor pressure changes are detected in cystometrographic pressures after the surgeries. The postoperative complications that will lead to reoperation will be infection, recurrent descent or incontinence, implant extrusion, chronic pelvic pain, and total retention. Operative and perioperative complications (six weeks after the procedures) described after TVM vs mTVM will be collected; overall frequency within all the cases will be calculated and severity will be graded using the IUGA classification comprising all the follow-up periods [27].

The subjective cure for prolapse and incontinence will be measured with a significant enhancement of the Pelvic Organ Prolapse/Urinary Incontinence Sexual Questionnaire (PISQ-12) and Pelvic Floor Distress Inventory (PFDI) scores. The PISQ-12 and PFDI are validated to assess the impact of SUI symptoms on quality of life and sexuality and relate well to the prolapse symptoms. Previous research has demonstrated that the questionnaires correspond well with grade of prolapse and urodynamic findings [5, 13, 17]. Our research group has assessed the validity of the questionnaires in screening for subjective genitourinary symptoms (unpublished data). To guarantee blinding of the tertiary outcome, the participant will complete the questionnaire without the outcome assessor present and seal it in an envelope, which will be given to research staff. The subjective outcome assessment is largely performed by participant-completed questionnaire, thus avoiding interviewer bias.

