### Statistical analyses

Analysis of the patients will follow the CONSORT flow diagram (Fig. 1) through the phases of the study (enrollment [assessed, excluded, randomized], allocation [control group and experimental group with intervention received or not received], follow-up [lost to follow-up, discontinued intervention] and analysis) [30].

All statistical analyses will be conducted using SPSS software version 22 (IBM, Armonk, NY, USA). All tests will be two-sided and significance will be set at *P* < 0.05. Efficacy measurements were adjusted by intention-to-treat analysis. Missing values will be replaced using the last observation carried forward (LOCF) method. No subgroup analyses are planned. Standard deviations, 95% confidence intervals, and median will be used for the descriptive analyses. Primary and secondary outcome analysis: the Chi-square test or Fisher’s exact test will be employed to identify any objective outcome differences among groups.

Generally, continuous data will be checked for normality using the Shapiro–Wilk test. If the normality assumption is violated, then PISQ-12 and PFDI scores as tertiary outcomes will be normalized by log transformation (log10(x)). Univariate-repeated measure analysis of variance (ANOVA) will be used to determine the secondary outcome between and within the two groups (mTVM, TVM group) at six endpoints (before intervention and during follow-up clinical appointments 1–5 following intervention). Mixed design ANOVA will be carried out to determine the effects of the modified operation on subjective cure rate for POP and SUI, and the Bonferroni post hoc test will be used to test the difference between means. All statistical analyses will be completed after the final measurement of the last patient during the last clinical appointment after intervention. The repeated measure design with seven points in time allows us to monitor how patients change over time in both short-term (before/during intervention) and long-term situations (before/after intervention).

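### The subjective cure rate is defined by a score enhancement and analysed by comparing means, so the planned analysis yields no proportion of women cured

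*Protocol article*

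**What the plan says.** Three places in the protocol article bear on this outcome.

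- **Abstract, Methods.** The secondary endpoints include "subjective prolapse and incontinence cure rates reported by questionnaires".
- **Secondary and tertiary endpoints.** The definition reads: "The subjective cure for prolapse and incontinence will be measured with a significant enhancement" of the PISQ-12 and PFDI scores. It gives no cut-off, no rule that classifies an individual woman and no visit.
- **Statistical analyses.** The method is stated as follows: "Mixed design ANOVA will be carried out to determine the effects of the modified operation on subjective cure rate for POP and SUI". Means are then compared post hoc with a Bonferroni correction. The questionnaire scores are to be log10-transformed if they are not normally distributed. For proportions, the same section says that "the Chi-square test or Fisher’s exact test will be employed to identify any objective outcome differences among groups"; subjective cure is not named there.

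The objective endpoints, under Primary endpoints, do have rules. For incontinence: "Anti-incontinence efficacy is classified as no further SUI, as diagnosed by cough tests and urodynamic examinations". For prolapse repair: "a significant (> 3 cm) improvement during follow-up at points Aa, Ba, C, and D".

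**The concern.** A cure rate is the number of women cured divided by the number assessed. To obtain it, each woman must be classed as cured or not cured. The article instead defines subjective cure by an enhancement of scores and assigns it a model for means. A difference in means, on the raw or the log scale, describes a group; no count of cured women comes out of it.

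At stake is what may be concluded. The Hypothesis section puts the questionnaire into the alternative hypothesis for the primary outcome, so these results may stand beside the headline continence claim. If *significant* is taken as P < 0.05, a shift in a mean could be written up as subjective cure. Whether it reaches P < 0.05 depends partly on how many women were enrolled.

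**Working it through.** **Step 1. Endpoint against analysis.** The article gives no figure for subjective cure to reproduce; its sample size concerns objective SUI cure only. The check is therefore mainly textual.

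| Element | Objective SUI cure | Subjective cure |
|---|---|---|
| Named as | cure rate | cure rate (Abstract; Statistical analyses) |
| Rule for each woman | no further SUI on cough test and urodynamics | none |
| Analysis | chi-square or Fisher | mixed design ANOVA, Bonferroni tests of means |
| Quantity produced | two proportions | mean scores by arm and visit |

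The first column is coherent from top to bottom. In the second, the quantity produced is not the quantity named.

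**Step 2. How small a mean change could count, if *significant* means P < 0.05.**

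Inputs:
- Two-sided 0.05 (Statistical analyses).
- 65 per arm (Abstract) or 81 per arm (Sample size calculation).
- Six questionnaire occasions: baseline and five follow-ups (Table 1; Statistical analyses). Pairs of occasions: 6 × 5 / 2 = 15.
- Assumption: Bonferroni is applied over all 15 pairs. The article does not say which comparisons it covers.
- No score SD is given, so results are in SD units. A t-test boundary stands in for the ANOVA post hoc test.

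Within an arm, the smallest significant mean change is t(1 − α/2, n − 1) / √n, in SDs of the change score:
- α = 0.05/15 = 0.0033: n = 65, 3.049 / 8.062 = 0.378; n = 81, 3.026 / 9 = 0.336.
- For comparison, unadjusted α = 0.05: n = 65, 1.998 / 8.062 = 0.248; n = 81, 1.990 / 9 = 0.221.

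Between arms, unadjusted, the smallest significant difference is t(0.975, 2n − 2) × √(2/n):
- n = 65: 1.979 × 0.1754 = 0.347.
- n = 81: 1.975 × 0.1571 = 0.310.

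**Step 3. Why a mean change does not fix a rate.** Assume normally distributed changes and a mean change of 0.378 SD, just significant after Bonferroni with n = 65. The share of women whose own change exceeds a threshold c is 1 − Φ(c − 0.378). The thresholds are assumed for illustration only.

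| Assumed threshold c (SD of change) | Share passing at mean change 0.378 | Share passing with no mean change |
|---|---|---|
| 0.5 | 45% | 31% |
| 0.8 | 34% | 21% |
| 1.0 | 27% | 16% |

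The same significant result is compatible with 27% to 45% of women passing, depending on a threshold that the article does not state.

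**The case against.** **The word *significant* may be a magnitude.** Under Primary endpoints the article uses it for an improvement of more than 3 cm. Read the same way, subjective cure would mean a sizeable score improvement, and only the cut-off would be missing, which a condensed article may leave to the full protocol. This stands in part: P < 0.05 is one reading, not the established one. It does not rescue the plan, because even with a cut-off the assigned analysis compares means, and a rate would need a different test.

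**The chi-square sentence covers secondary outcomes.** It is introduced as the primary and secondary outcome analysis, and the Abstract lists subjective cure as secondary. But the sentence is confined to objective outcomes, and the subjective rate is given its own method in the next paragraph.

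**The arms are compared.** A reader might infer that the between-arm question is lost, or replaced by setting two within-arm P values side by side. The text does not support that. A mixed design has arm as a between-subjects factor and time as a within-subjects factor, so arm and arm-by-time effects are its direct output, and the stated aim is the effect of the modified operation. This objection stands in full.

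**The outcome is low in the hierarchy.** The body of the article treats the questionnaire scores as tertiary, and the sample size rests on objective SUI cure. That limits the weight of the point but does not remove the mismatch.

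**Conclusion.** The point holds as a mismatch between the named endpoint and its stated definition and analysis. It is not merely a missing threshold, since the article fixes the test as well as the label. This conclusion rests on the text alone and needs no numerical assumption.

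The numerical part is conditional. On the statistical reading of *significant*, a mean change of about 0.38 SD within an arm of 65 (0.34 SD with 81), or a between-arm difference of about 0.35 SD (0.31 SD), could be reported as cure. Without a score SD or a minimal important change, the documents cannot show whether changes of that size matter to patients.

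Two further inferences go too far. The boundary of about 0.25 SD (0.22 SD with 81) comes from an unadjusted paired test, whereas the plan specifies Bonferroni post hoc tests. And one cannot say that both arms would be declared cured: the article reports no PISQ-12 or PFDI change for either operation.

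**What to change.** In the Abstract, in Secondary and tertiary endpoints and in Statistical analyses, rename the outcome as the between-arm difference in PFDI and in PISQ-12 score, adjusted for the baseline score, with a 95% confidence interval. Make 12 months the main visit. Questionnaires are already scheduled then (Table 1), and the allocation section says women are told their arm after completing the 12-month forms, so it is the last visit before that planned disclosure. The repeated-measures model may stay as supporting analysis.

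If a cure rate is to be kept, define it as yes or no for each woman at that visit, with the criterion stated for each questionnaire, and compare the arms with the chi-square or Fisher test already planned for the objective outcomes.

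No new data are needed under either option. The first gives up the word cure for the scores. The second keeps it but loses some information by dichotomising, and obliges the sponsor to commit to a cut-off.

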### Trial interventions

Participants will receive the allocated intervention, either the original TVM operation or mTVM surgery. The surgical interventions will be delivered by two surgeons with expertise in the specific intervention and subspecialized in urogynecology. They will not assess the measurement outcomes. Further details on the interventions are provided below.

### Original transobturator four-arm transvaginal mesh

Original transvaginal subvesical mesh operations will be performed as described earlier by Sergent et al. [13, 17]. The operative technique is described in detail in another study [28]. The routine surgical technique will consist of a longitudinal incision of the anterior vaginal wall throughout its thickness from 3 cm below the urethral meatus to the cervix. The posterior part of the mesh will be anchored to the anterior side of the cervix using two non-absorbable Prolene® 2-0 sutures (Ethicon, Issy-les-Moulineaux, France), while the mesh will then be spread by securing its anterior parts beneath the bladder neck using two or three Monocryl® 2-0 absorbable sutures (Ethicon, Issy-les-Moulineaux, France). Conventional instruments will be employed for the original TVM procedure.

### Modified intervention surgery

In the modified surgical technique, the prosthesis is placed between 1.5 cm below the urethral meatus and the cervix and the anterior part of the mesh is anchored with a stabilizing suture to the periurethral tissue at the level of the mid-urethra to elevate the middle part of the urethra, leading to potentially more effective anti-incontinence. An additional document file presents the intervention (detailed description of the mTVM) in detail (see Additional file 2).

### Assessment of safety: postoperative complications/reoperations

In the current study, there are no anticipated risks or inconveniences, as the examinations and intervention employed are well-known and widely used in pelvic floor defect surgery. The modification to the TVM surgery does not carry a higher risk for patients than that of the original TVM in the setting of a fully equipped operation theatre. This makes the immediate detection and treatment of adverse events possible. Also, after leaving the operation room, all patients will be closely monitored for the occurrence of potential (severe) adverse events (short-term postoperative complications) on the postoperative intensive ward. Moreover, the inclusion of each individual patient in the study is indicated in the electronic hospital information system and, hence, is visible to all physicians and nurses involved in the care of the patient. This facilitates the reporting of (severe) adverse events to the principal investigator. The principal investigator will report suspected unexpected serious adverse reactions to the Institutional Review Board.

## Statistical methods

### Hypothesis

Alternative hypothesis for primary outcome: it is hypothesized that the group undergoing the modified transvaginal mesh operation will have a statistically higher improvement of continence measured by gynecological and urodynamic examination, and from the questionnaire administered before and after the intervention phase.

#### Sample size calculation

As we have newly developed the modification to the prosthesis surgery, an exploratory pilot study was designed to evaluate the feasibility of the modification to the mesh for the treatment of SUI. Twenty patients with SUI and POP were recruited for a mTVM operation by the same two senior surgeons who are conducting this randomization study. The sample size calculation study was designed based on preliminary data on the 20 patients. The newly developed technique yielded an objective SUI cure rate of 92% as opposed to 72% for the original TVM published by Sergent et al. [13, 17]. Sample size calculations were performed with G*Power software [29], using the statistical model for an χ^2^ approach. Consequently, sample size was estimated theoretically and an effect size of = 0.1, indicating a small effect, will be accepted. The sample size was calculated for the primary outcome of the SUI cure rate with the following assumptions: α = 0.05, power (1–β error probability) = 0.8, number of groups = 2. Based on these assumptions, a total sample size of *N* = 130 was estimated. In anticipation of dropouts (10%: *n* = 16) or a violation of protocol (10%: *n* = 16), a final sample size of *N* = 162 (81 participants per group) results.

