Therefore, the research group developed a modification to the transobturator four-arm TVM [13, 17] to increase its anti-incontinence effect. While the sling is located beneath the mid-urethra, the TVM elevates the distal part of the anterior vaginal wall [13, 17]. In the original TVM, the posterior part of the mesh is anchored to the anterior aspect of the cervix and the anterior arms are spread under the bladder neck with stabilizing sutures. We hypothesize that the original TVM operation can be followed by residual SUI since the strengthening of the back arms may result in a backward dislocation of the entire mesh. The posterior movement of the mesh allows the dorsal rotation of the urethra since the mid-urethra is not suspended. The proposed modification to the original surgical procedure includes the suture of the anterior part of the mesh to the mid-urethra to prevent the mesh sliding. We think that the appropriate elevation of the mid-urethra would thus occur with the anterior arms and that would achieve a more effective anti-incontinence. The pubourethral ligament is usually loose in SUI, but the anchored mesh would theoretically normalize its function and stabilize the urethra. Intra- and postoperative complication rates would be expected to be similar to those with the original four-arm TVM, but the modified TVM with the anchoring suture would be slightly superior with respect to POP repair and remarkably more effective in SUI correction. In our preliminary study, the anterior fixing of the TVM to the mid*-*urethra demonstrates as high an efficacy of anti-incontinence as 96.8% and an enormously reduced recurrence prolapse rate of 3.2% in (unpublished data). The mesh extrusion rate is particularly low and this may be due to the fact that the stabilizing sutures exert a lack of “folding/wrinkling” of the edge of the mesh, preventing a lifting up of the mesh which does not compress the mucosa and derange the periprosthetic vasculature.

A further modification to the TVM surgery is that the positioning of the mesh will occur 1.5 cm below the urethral meatus, leading to an elevation of the entire anterior vaginal wall including the anterior and middle compartments as well. By contrast, the original TVM surgery does not prevent anterior compartment prolapse [13, 17].

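### The 92% cure rate used to size the trial is not a possible proportion of the 20 pilot patients it is attributed to, and it is not reconciled with the 96.8% given in the Background

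*Protocol article*

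**What the plan says.** The Sample size calculation section of the protocol article describes one pilot: "Twenty patients with SUI and POP were recruited for a mTVM operation by the same two senior surgeons" who operate in the trial. It names that pilot as the planning source: "The sample size calculation study was designed based on preliminary data on the 20 patients". It then gives the contrast: "The newly developed technique yielded an objective SUI cure rate of 92% as opposed to 72% for the original TVM", the 72% being taken from a published series. No numerator, number assessed or follow-up time accompanies the 92%. With α = 0.05 and power 0.8, the section arrives at N = 130, raised to 162 for dropout and protocol violation.

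The Background cites an unpublished preliminary study of the same modification, which "demonstrates as high an efficacy of anti-incontinence as 96.8% and an enormously reduced recurrence prolapse rate of 3.2" per cent. It gives no denominator and does not say whether these are the 20 pilot women.

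**The concern.** All 20 pilot women are described as having SUI, so a reader expects all 20 in the denominator of an SUI cure rate. No whole number of cures out of 20 gives 92%. The article also offers a second mTVM continence rate, almost five points higher, without linking the two.

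The 92% is one side of the 92% versus 72% contrast on the outcome that sizes the trial. If its count is unknown, the reader cannot tell whether 130 evaluable women give the stated power.

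**Working it through.** **Inputs.** Sample size calculation: pilot n = 20, mTVM 92%, original TVM 72%, α = 0.05, power 0.80, N = 130 (65 per arm). Statistical analyses: two-sided tests, chi-square or Fisher's exact. Background: 96.8% and 3.2%.

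**Step 1: can 92% be reproduced from 20 patients?** Let m be the number not cured out of n. A rate that rounds to 92% needs m/n between 7.5% and 8.5%.
- n = 20 would need m between 1.5 and 1.7, so no whole number works. The neighbours are m = 2 (18/20 = 90%) and m = 1 (19/20 = 95%).
- m = 1 needs n between 1/0.085 = 11.8 and 1/0.075 = 13.3. This gives 11/12 = 91.7% and 12/13 = 92.3%. If the figure was truncated instead of rounded, 13/14 = 92.9% also fits.
- m = 2 needs n between 23.5 and 26.7, that is 22/24, 23/25 or 24/26, all larger than the pilot.

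So 92% is not a proportion of 20. Within the pilot it needs about 12 or 13 women assessed.

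**Step 2: can 96.8% come from 20 patients?** To one decimal, m/n must lie between 3.15% and 3.25%. With m = 1, n lies between 30.8 and 31.7, so n = 31 (30/31 = 96.8%, 1/31 = 3.2%). The highest rate below 100% with n up to 20 is 95%. The Background figure therefore needs at least 31 patients.

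**Step 3: what depends on the rate.** With control p₁ = 0.72, mTVM p₂, d = p₂ − p₁, p̄ their mean and n per arm:

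power = Φ{[d√n − 1.960√(2p̄(1−p̄))] / √(p₁(1−p₁) + p₂(1−p₂))}

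n = [1.960√(2p̄(1−p̄)) + 0.842√(p₁(1−p₁) + p₂(1−p₂))]² / d²

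- At 92%: power = Φ[(0.20 × 8.062 − 1.065)/0.525] = Φ(1.04) = 85.2%
- At 90%: power = Φ[(0.18 × 8.062 − 1.087)/0.540] = Φ(0.67) = 75.0%
- At 95%: power = Φ[(0.23 × 8.062 − 1.029)/0.499] = Φ(1.65) = 95.1%

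| mTVM rate | Total N for 80% | Power, 65 per arm | Fisher's exact, 65 per arm |
|---|---|---|---|
| 90% (18/20) | 148 | 75.0% | 69.1% |
| 92% (as stated) | 114 | 85.2% | 81.4% |
| 95% (19/20) | 80 | 95.1% | 94.3% |
| 96.8% (Background) | 66 | 98.0% | not computed |

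For the within-pilot readings, 11/12 gives 83.7% power and 12/13 gives 86.5%.

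**Step 4: precision.** Exact 95% intervals are 68–99% for 18/20, 75–99.9% for 19/20, 64–99.8% for 12/13 and 83–99.9% for 30/31. The first and third include 72%; the other two do not.

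**The case against.** The article says that 20 women were recruited, not that all 20 had the objective outcome assessed. If 12 or 13 completed the tests, 92% is a genuine pilot result. This stands. A reader might infer that 92% cannot have come from the pilot at all, and the documents do not support that.

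A reader might also infer that planning rested on a different or mixed population. That does not follow either. Fewer women assessed could simply mean missed urodynamic tests or incomplete follow-up, and the section says plainly that the 20 had SUI and POP.

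Nor is the Background a direct contradiction. It never says that its series is the pilot, and its measure (anti-incontinence efficacy) may not be the objective cure rate. Two series or two definitions could give two rates. What remains is a lack of reconciliation.

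On size, 92% lies between the attainable values, and only the lower one falls short of 80%, by about 5 points. Wide intervals that include 72% show only that a small pilot is imprecise. The inflated total of 162 also exceeds the 148 needed at 90%. If all 81 per arm were analysed, power at 90% would be Φ[(0.18 × 9 − 1.087)/0.540] = Φ(0.99), about 84%. However, the 32 extra women are there to cover losses, and the stated power refers to 130.

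Finally, correcting 92% does not repair the whole calculation. The section also says "an effect size of = 0.1, indicating a small effect, will be accepted". At 0.1 a one-degree-of-freedom chi-square test would need 785 patients. That is a separate problem.

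None of this clears the text. The article itself puts n = 20 and 92% together, so the mismatch is not a product of condensation. If only 12 or 13 women were assessed, 7 or 8 of the 20 are missing from the rate without mention.

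**Conclusion.** The point holds in a limited form. The 92% does not match its stated source of 20 patients unless only about 12 or 13 were assessed, which is not stated. The 96.8% in the Background needs at least 31 patients, and the two mTVM rates are left unreconciled.

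The consequence is a planning input without a traceable count. Power for 130 evaluable women runs from about 75% to 95% across the two attainable 20-patient rates, against a target of 80%. This assumes a 72% control rate, 65 analysed per arm and the pooled two-sided chi-square test; Fisher's test lowers the figures to 69% and 94%. It should be corrected, but it does not show that the trial is underpowered or that the planning population differs from the one described.

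**What to change.** In the Sample size calculation section, replace 92% with the actual number cured over the number assessed among the 20 pilot women, or state that 92% is a planning assumption and not the pilot result. Say whether the preliminary study in the Background is the same women, give its count, and correct whichever figure is wrong. Restate the power for N = 130 at the corrected rate.

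The cost is a check of the pilot records, a reworded sentence in each place and one recalculation. The downside is that the stated power may become somewhat less favourable: at 18/20 it falls to about 75%, and the sample size would then need another look.

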## Background

Demand for pelvic organ prolapse (POP) and stress urinary incontinence (SUI) surgery is expected to increase due to an expanding rate of obesity among elderly women. POP is defined as the protrusion of the pelvic organs from the normal anatomical location toward or through the vaginal opening; the current prevalence of symptomatic POP is in the range of 3–8% [1, 2]. SUI, classified as involuntary loss of urine during physical activities and a resultant increase in intra-abdominal pressure, is also highly prevalent, reaching as high as 24.8% [3].

Also of note, one-fifth of women in the United States receives surgery either for SUI or for POP [4], where the cumulative risk for SUI surgery is 13.6% and that for POP surgery is 12.6% [4]. Both pathologic conditions develop in > 50% of the women affected [5]. Synthetic transvaginal mesh (TVM) has been increasingly employed in the treatment of POP and tension-free slings are useful in the management of incontinence. Synthetic mesh during repair has principally been used due to higher efficacy compared to that of native tissue repair and resorbable mesh; however, complications appear to be more prevalent [6–9]. Common complications include mesh extrusion, chronic pelvic pain, dyspareunia, and infection [7–10]. The anti-SUI efficacy of the prosthetic placement is barely 72–83% [11–13]; however, it is assumed that a combination of a synthetic mesh with the sling operation [5, 14–16] will substantially increase the cure rate for concomitant SUI.

Despite the increased consideration of the combined surgery for both genitourinary pathologies in one session, there is a lack of consensus on the optimal treatment. It is supposed that a combined operation with mesh and sling is highly effective for the treatment of POP and SUI; however, the complication rate is elevated [5, 14–16].

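### The sample size paragraph gives two incompatible effects for one calculation: the stated effect size of 0.1 would need 785 women, while the stated cure rates of 72% and 92% (w = 0.26) support a total near 130

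*Protocol article*

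**What the plan says.** All the relevant text is in two sections of the protocol article.

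- **Sample size calculation, the rates:** "The newly developed technique yielded an objective SUI cure rate of 92% as opposed to 72% for the original TVM". The 72% is attributed to the published reports of the original operation, and "The sample size calculation study was designed based on preliminary data on the 20 patients".
- **Sample size calculation, the model:** G*Power, "using the statistical model for an χ^2^ approach", for the SUI cure rate.
- **Sample size calculation, the effect size:** "an effect size of = 0.1, indicating a small effect, will be accepted".
- **Sample size calculation, the other inputs:** "α = 0.05, power (1–β error probability) = 0.8, number of groups = 2".
- **Sample size calculation, the result:** a total of 130 is presented as following from these assumptions. It is raised to 162 (81 per group) for dropout and protocol violation.
- **Statistical analyses:** "All tests will be two-sided". Objective outcomes are to be compared by chi-square or Fisher's exact test.

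**The concern.** One calculation is given two different effects. The first is a pair of cure rates 20 percentage points apart. The second is a standardised effect of 0.1, described as small. They cannot both be the basis of the same N, and the paragraph presents the second as a planning assumption that leads to 130.

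What is at stake is the stated sensitivity of the trial on the only endpoint for which it is sized. As written, a reader is told that about 130 evaluable women give 80% power for a small effect. Someone who relied on that could take a non-significant result as evidence against a small benefit, when the trial would have had roughly a one-in-five chance of detecting one. The calculation also cannot be reproduced from the inputs it lists.

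**Working it through.** **Inputs.** From Sample size calculation: effect size 0.1, alpha 0.05, power 0.80, two groups, chi-square model, rates 72% and 92%, N = 130, inflated to 162. From Statistical analyses: two-sided tests, chi-square or Fisher's exact. Allocation is 1:1 (Concealment of group allocation from participants). The article does not name the effect-size measure. I take it as Cohen's w, the usual measure for a chi-square model. Two groups by cured/not cured gives 1 degree of freedom.

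**Step 1: try to reproduce 130 from effect size 0.1.** For a 1-df chi-square test the noncentrality is λ = N × w². Power of 80% at alpha 0.05 needs λ ≈ (1.960 + 0.8416)² = 7.849.

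- Required N = 7.849 / 0.1² = 784.9, so 785. The figure of 130 is not reproduced; the ratio is 785/130 ≈ 6.
- At N = 130, λ = 130 × 0.01 = 1.30 and power is 20.7%.
- At N = 162, λ = 1.62 and power is 24.7%.

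**Step 2: other readings of 0.1.**

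| Reading | Total N for 80% power |
|---|---|
| w = 0.1, 2 df | 964 |
| w = 0.1, 3 df | 1091 |
| w = 0.1, one-sided equivalent | 619 |
| 10-point difference, 72% vs 82%, two-sided | 554 |
| 10-point difference, 82% vs 92%, two-sided | 354 |
| Repeated-measures ANOVA, f = 0.1, between groups, 2 to 7 time points | 592 down to 452 |
| Repeated-measures ANOVA, f = 0.1, interaction, 2 to 7 time points | 200, 164, 138, 122, 110, 100 |

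The ANOVA rows assume a correlation of 0.5. The interaction row passes from 138 to 122, so some other correlation could be chosen to give about 130. But the article names a chi-square model and a binary endpoint and states no correlation.

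**Step 3: the stated cure rates.** With equal groups, w = (difference / 2) / √[p̄(1 − p̄)], where p̄ is the mean of the two rates.

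- p̄ = (0.72 + 0.92)/2 = 0.82, so w = 0.10 / √(0.82 × 0.18) = 0.10 / 0.3842 = 0.260.
- Chi-square: N = 7.849 / 0.260² ≈ 116 (with w unrounded, 0.2603).
- Pooled two-proportion formula: 114 in total; with continuity correction, 134.
- Fisher's exact test, by full enumeration: power is 79.8% at 63 per arm and 80.6% at 64 per arm, so 128 in total.

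Power for 72% vs 92% at the planned sizes:

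| Women per arm | Chi-square (noncentral) | Fisher's exact |
|---|---|---|
| 65 (total 130) | 84.3% | 81.4% |
| 81 (total 162) | 91.2% | 89.8% |

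**Step 4: what 130 can detect.** The smallest w with 80% power is √(7.849/130) = 0.246, and √(7.849/162) = 0.22 with 162. With a control rate of 72%, w = 0.246 is about 72% vs 91.1%: 0.0955 / √(0.8155 × 0.1845) = 0.246. By comparison, w = 0.1 is about 72% vs 80.5%: 0.0425 / √(0.7625 × 0.2375) = 0.0999. The two statements therefore differ by roughly 19 points against 8.5 points.

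**Step 5: optional sensitivity information.** Background gives a range for mesh alone: "The anti-SUI efficacy of the prosthetic placement is barely 72–83" per cent. At its upper end, 83% vs 92%, w = 0.045 / √(0.875 × 0.125) = 0.136. Power at 65 per arm is then 34% by chi-square and 25% by Fisher's exact test.

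**The case against.** The best defence is that 0.1 is a slip of wording and the sample size is sound. The design rates are printed in the same paragraph, one of the two planned tests reproduces 130 to within two women, and the report will carry confidence intervals. Most of this stands. It does not rescue the 0.1 statement, which is presented as an assumption behind N and is wrong by a factor of about six in sample size. Nor does the named chi-square model give 130 from either effect (785 or 116).

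Four stronger readings are tempting, and the documents do not support them.

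- **That the trial is underpowered and needs 785 women.** The 21% is conditional on a true w of 0.1. For the stated rates, power at 65 per arm is 81% to 84%.
- **That 92% is impossible in a pilot of 20.** No whole count out of 20 gives 92%, but the article says only that 20 were recruited and gives no evaluable number; 11/12 and 12/13 both round to 92%. For the same reason a confidence interval around the pilot rate settles nothing: it needs a numerator the article does not give. An assumed 18/20 gives 68% to 99%, which includes 72%, while 19/20 gives 75.1% to 99.9%, which excludes it.
- **That 92% contradicts the Background,** where an unpublished preliminary study "demonstrates as high an efficacy of anti-incontinence as 96.8" per cent. The article never says that this study is the 20-patient pilot.
- **That 72% was picked as the bottom of the cited range.** It is taken from the reports that define the control operation, which is a defensible choice. Power at 83% is useful to show, but its absence is not an error.

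**Conclusion.** The point holds as an internal inconsistency in a stated design figure. Effect size 0.1 with the listed alpha, power and chi-square model needs 785 women, not 130, and has about 21% power at 130 (25% at 162). The cure rates in the same paragraph are w = 0.26 and support a total near 130: 116 by chi-square, 128 by Fisher's exact. The 0.1 is most likely the wrong item and N can stand. The article does not say how 130 was actually obtained, so that attribution remains an inference.

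The conclusion assumes that 0.1 is Cohen's w with 1 df. The alternatives in Step 2 do not restore 130 without an input the article does not state. The 81% to 84% power holds only if the true rates are 72% and 92% and 130 women are evaluable.

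**What to change.** In Sample size calculation:

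1. Delete the statement that a small effect size of 0.1 is accepted.
2. State the design effect as 72% versus 92% (w about 0.26) and name the test used for sizing.
3. State that 130 evaluable women give about 84% power by chi-square or 81% by Fisher's exact test at two-sided alpha 0.05, and that the smallest w detectable with 80% power is about 0.25.
4. Give the numerator and denominator behind the pilot rate of 92%. This is a request for clarity, not the correction of a shown error.
5. Optionally, add power at 83% versus 92% (34% by chi-square, 25% by Fisher's exact at 65 per arm) as sensitivity information.

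If w = 0.1 really is the target, rewording is not enough: about 785 women would be needed before any allowance for dropout, and the sponsor should say so.

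Otherwise the cost is a few sentences. No extra patients are needed, and recruitment and analysis do not change. The only downside is that the stated sensitivity becomes less favourable. Statistical analyses places all analyses after the last patient's final appointment, so the text can be corrected before any result is known.
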